### Study treatments

Participants will be randomized to yoga classes, therapeutic exercise classes or receipt of a self-care book. Both the yoga and exercise interventions will consist of 12 weekly 75-minute classes supplemented by home practice. The dose of yoga in this study was chosen because it was found effective in our previous trial back pain [19]. Conceivably, the "optimal dose" of yoga could differ from the amount of yoga we will provide, but we are unaware of studies that have examined this issue. Participants will be asked to report their weekly home practice on pre-printed home practice logs. For legal and ethical reasons, all participants will continue to have access to the services normally available under their health insurance plan, regardless of the intervention they are assigned. The treatments are described below.

#### A. Yoga

We will use viniyoga, a therapeutically-oriented style of yoga that emphasizes safety, is easy to learn, and has rigorous teacher training standards, as the basis of our intervention. Because viniyoga focuses on the purpose of each posture, rather than on its precise form, it tailors the postures to abilities of each individual's body. This emphasis on safe performance of individual poses and careful sequencing of the poses minimizes the risk of injury and discomfort. Viniyoga also emphasizes special breathing techniques that reduce stress and increase awareness of the body, considered important for reducing injury [21].

Our yoga intervention ("Yoga for Backs") [19] includes six yoga posture sequences created using the principles of viniyoga [25] and designed for people with low back pain who have no previous experience with yoga. The postures for each class were selected, with minor adaptations, from a core of 17 relatively simple postures (Table 3). Each posture sequence will be repeated in two successive classes with every other class having a different focus (i.e., relaxation; developing strength, flexibility and large muscle movement; asymmetrical postures; strengthening the hip muscles; lateral bending; integration and customizing a personal practice). All classes will emphasize the use of postures and breathing for managing low back symptoms.

**Table 3 T3:** Content of Each Yoga Class

	Class Number					
**Yoga Class Components**	**1 and 2**	**3 and 4**	**5 and 6**	**7 and 8**	**9 and 10**	**11 and 12**

Introductory Breathing Exercise	x	x	x	x	x	x

Cobra posture and variations	x	x	x	x	x	x

Knee to chest and variations	x	x	x	x	x	x

"Wheel" posture variations	x	x	x	x	x	x

Bridge posture variations	x	x		x		x

Supine butterfly posture	x	x	x	x		

Extended leg with variations		x	x	x	x	x

Warrior posture variations		x				x

Standing forward bend			x		x	x

Kneeling forward bend with variations		x	x		x	

Chair pose		x	x			x

Lying twist/lying lateral		x			x	x

Swimmer's posture with variations			x		x	x

Extended side stretch			x			

Lunge				x		

Lying side hip strengtheners				x		

Kneeling lateral posture					x	

Standing lateral posture					x	

Deep Relaxation	x	x	x	x	x	x

Final Breathing Exercise	x	x	x	x	x	x

Each class will include an initial breathing exercise, a sequence of 5 to 11 postures, a guided deep relaxation and a final breathing exercise. Most postures will not be held for prolonged periods but will be repeated 3 or 6 times sequentially in a flow. In addition to the introduction of new poses in each new sequence, many poses and basic concepts will be repeated throughout the series to facilitate and encourage home practice. Participants will be asked to practice every day for 20 minutes to maximize the benefit of the intervention. At the end of the 1^st^, 4^th^, 7^th^, 9^th ^and 11^th ^classes, they will receive a printed handout outlining the sequence of poses and a corresponding CD to be used for their home practice. The CD will assist them in practicing the postures with the appropriate mental focus.

#### B. Conventional therapeutic exercise

The exercise intervention will be identical to the yoga classes in terms of length of classes (75 minutes), number of classes (12) and amount of physical exertion required (stretching and strengthening exercises only, with no extreme movement). Most of the class will involve conventional stretching exercises that are appropriate for patients with chronic back pain, including a comprehensive set of exercises that stretch all the major muscle groups, with an emphasis on the trunk and legs. The intervention will include all 12 stretching exercises used in the exercise intervention of a previous study [19] (i.e., gastrocnemius, soleus, quadriceps, posterior and inferior shoulder, upper trapezius, hip flexor, back extension, back rotation, hamstrings, hip external rotators, back flexion), plus 3 additional stretches (hip internal rotators, hip adductors and hip flexion). Each stretching exercise will be held for approximately 60 seconds and repeated once. In addition to a complete set (15) of full-body stretches, the class will begin with a five minute warm-up period consisting of basic aerobics steps (i.e., one minute each of walking in place, marching, lateral shuffling, turning and reaching, and box step) and will also include four exercises from our previous study that strengthen the back, abdomen and hips (i.e., squats, crunches, oblique crunches, back extensions) [19]. Over the 12-weeks of class, the number of weekly repetitions of each strength exercise will be increased from 8 to 30 in increments of two. Specific strength exercises will be practiced in separate sets of 5 to 10 repetitions. For example, if 16 repetitions of all 10 of the strength exercises are to be performed, 8 repetitions of each of the 10 exercises will first be performed followed by another 8 repetitions. Participants will be asked to practice every day for 20 minutes to maximize the benefit of the intervention. Printed handouts will be provided to facilitate practice. In addition, a DVD demonstrating all the exercises will be provided to assist participants in practicing safely.

#### C. Self-care book

Participants in this group will be mailed a copy of *The Back Pain Helpbook*, a 224-page evidence-based book on self-care for back pain. The book includes information on causes of back pain, initiating a comprehensive fitness and strength program, and appropriate life-style modification and guidelines for managing flare-ups [24]. We believe that providing these materials may mitigate the disappointment among those randomized to "continued usual care". Such disappointment could conceivably bias reports of symptom severity and dysfunction and result in higher rates of loss to follow-up. Sending these participants a book also allows us to describe our study as a comparison of different lifestyle interventions, which helps create more uniform expectations for the different interventions.

#### Class sites

The yoga and therapeutic exercise classes will be offered in large, quiet classrooms at Group Health facilities that are centrally located and provide easy access for persons with physical limitations.

#### Class instructors

All our yoga instructors' will be certified in viniyoga, which has one of the most comprehensive yoga teacher training programs in the West. Training takes at least three years to complete and leads to certification at the highest level (500 hours) by the Yoga Alliance, the group that has established voluntary national standards for yoga teachers. All certified viniyoga instructors are trained to work with people suffering from back pain. [name], our local yoga consultant who helped develop the intervention for our previous study [19], will help us select qualified instructors and will train them to the protocol.

We will require our exercise class instructors to be licensed physical therapists who have previous experience teaching groups. [name], the physical therapist who developed our "Healthy Backs, Healthy Lives" exercise class series and who will revise the exercise intervention for this study, will help us select qualified instructors and will train them to the protocol.

### Training and monitoring of class instructors

All of the yoga and exercise instructors will need to agree to adhere strictly to the treatment protocol and to complete our training programs for yoga (to be taught by trial Principal Investigator [name] and yoga expert [name]) and exercise (to be taught by [name] and exercise expert, [name]). This training will include a thorough discussion of the class protocols for each intervention. There will be an opportunity for each instructor to practice leading a class as part of the training and to discuss any concerns they may have.

During the class series, [name] will be in weekly contact with the instructors and will inquire about positive experiences, adverse events, concerns raised by participants, ability to stay within the protocol, and any other questions that may arise. Research specialists will attend each of the classes to collect home practice information and take attendance. [name] will also attend at least one class in each series to ensure that instructors are adhering to the protocol.

### Assessment of outcomes

We will collect data on sociodemographic characteristics, back pain history, back outcome measures, treatment-related information, potential confounders, co-inventions, and a number of key psychological, physical and physiological factors that we hypothesized might mediate any effects of yoga on chronic low back pain (Figure 1). We will measure short-term (6-week and 12-week) outcomes to determine whether the classes have had any benefit prior to or immediately following their completion, and longer-term (26-week) outcomes to determine if such benefits persist and if participants are continuing to practice their new skills. These measures are summarized in Table 4, with the most important measures described in the text that follows.

**Table 4 T4:** Content of baseline and follow-up assessments

Measures	Baseline	6-Wk	12-Wk	26-Wk
**BASELINE INFORMATION**				

Sociodemographic characteristics	x			

Back pain history	x			

Expectations of treatment	x			

Knowledge of yoga and therapeutic exercises	x			

**CORE SET OF OUTCOMES FOR BACK PAIN STUDIES**				

* Roland Morris Disability Questionnaire (RDQ)(dysfunction)	x	x	x	x

* Bothersomeness of low back pain	x	x	x	x

Satisfaction with back care	x	x	x	

Disability days	x	x	x	x

Patient global rating of improvement		x	x	x

**TREATMENT-RELATED INFORMATION**				

Adverse experiences		x	x	x

Perceptions of yoga and therapeutic exercise classes, including instructors			x	

Adherence to assigned treatment, including home practice		x	x	x

**POTENTIAL CONFOUNDERS**				

Use of co-interventions: medications	x	x	x	x

Use of co-interventions: other treatments			x	x

Daily exercise and job-related activity	x	x	x	x

Smoking status	x			x

Lawsuits, workers compensation (initial exclusion)			x	x

Body Mass Index	x			x

**POTENTIAL MEDIATING VARIABLES**				

***Positively impacts cognitive appraisal***				

Fear avoidance	x	x	x	x

Self-efficacy	x	x	x	x

Conscious awareness of body	x	x	x	x

***Positively impacts affect and stress***				

Psychological distress	x	x	x	x

Perceived stress	x	x	x	x

Positive emotions	x	x	x	x

***Reduces physical impairment***				

Physical Impairment Index	x		x	

***Improves neuroendocrine function***				

Salivary cortisol	x	x	x	

Salivary DHEA	x	x	x	

* Co-primary outcome measures

A core set of outcome measures, covering five domains (back-related function, pain, general health status, work disability and patient satisfaction) has been recommended in a general review of outcomes assessments for evaluating treatments of spinal disorders [26]. Our choice of outcome measures closely follows these recommendations.

#### A. Primary outcome measures

The modified Roland-Morris Disability Questionnaire (RDQ) will be used to measure back-related patient dysfunction [27]. This instrument, which asks 23 yes/no questions selected because of their relevance for patients with back problems, takes approximately five minutes to complete [26]. The RDQ is one of the two most popular instruments used by back pain researchers for measuring function [28], has been found to be reliable, valid and sensitive to clinical changes [27,29-34], and is well suited for telephone administration [28].

Because there are individuals who are very bothered by even a small amount of pain and others who are not bothered by even moderate pain, we felt that the important outcome was not so much a difficult-to-interpret report of pain severity as is often used, but the extent to which participants' lives are affected by whatever level of pain they felt (i.e., how bothered they are by their symptoms). We therefore have chosen as our primary measure of symptoms a 0 to 10 scale of "symptom bothersomeness", where 0 represents "not at all bothersome" and 10 "extremely bothersome". Participants will be asked at baseline and during all follow-up interviews to rate how "bothersome" their back-pain has been during the previous week. This question has worked well in our previous studies with both mailed and telephone interviews [27,35,36]((and appears to have substantial construct validity, i.e., is highly correlated with measures of function and other outcome measures [37].

#### B. Potential mediating variables

We will measure a number of psychological, physical and physiological variables that our heuristic model (Figure 1) hypothesized could mediate any effects of yoga on low back pain. If yoga is superior to self care and/or to exercise, these will be included in analyses designed to address Aim 3.

##### a. Cognitive appraisal

Aspects of cognitive appraisal will be assessed with measures of fear avoidance, self-efficacy, and self-awareness.

*Fear avoidance *will be measured with the Tampa Scale for Kinesiophobia [38], a 17-item scale measuring back pain patients' fears of movement, exercise and serious underlying disease. We will use 10 of the 17 items from this scale, eliminating several items found confusing to participants or redundant [39]. This 10-item version retains acceptable internal consistency (Cronbach's alpha = 0.76), is easier and quicker to administer than the full form and has proved sensitive in detecting intervention effects in clinical trials [39].

We will measure *self-efficacy *using 5 of 8-items of the Arthritis Self-efficacy Scale [40], modified for back pain patients. This scale has been found to be both valid and reliable [40].

We will measure *awareness *specifically as conscious awareness of the body using two complementary and validated questionnaires, the Body Awareness Questionnaire [41] and the Body Responsiveness Questionnaire [42]. The Body Awareness Questionnaire contains 18-items that measure self-reported attentiveness to normal non-emotive bodily processes, including sensitivity to body cycles and rhythms, ability to detect small changes in normal function, and ability to anticipate bodily reactions. It has been found to have good internal consistency and test-retest reliability [41,42]. (The Body Responsiveness Questionnaire, a 7-item scale designed to measure responsiveness to bodily sensations, also has good internal consistency (Cronbach's alpha = 0.83) [42].

##### b. Affect and stress

We will measure psychological distress, perceived stress and positive states of mind.

*Psychological distress *will be measured with the 5-item Mental Health Index of the SF-36 [43]. This scale, which assesses general mental health, including depression, anxiety, behavioral-emotional control, and general positive affect, is brief and reliable and has shown good agreement with more comprehensive measures of mental health [44].

*Perceived stress *will be measured with the 10-item version of the Perceived Stress Scale [45], the most widely used self-report measure of psychological stress.

We will measure *positive states of mind *with the Positive States of Mind Scale, a 6-item scale that has good internal consistency (Cronbach's alpha ranges from 0.65 to 0.77) [46,47] and is inversely related to anxiety and to indicators of stress [46].

##### c. Physical impairment

We will measure physical impairment using Waddell's Physical Impairment Index, which includes the results of 7 physical tests (total flexion, total extension, lateral flexion, average straight leg raise, and bilateral straight leg raise, all measured in degrees; and spinal tenderness and sit-up, both measured as yes/no) [47]. The Index includes measures of both flexibility and strength. We will also be able to use each test as an independent measure of physical impairment.

##### d. Biomarkers of neuroendocrine function

We will measure *cortisol *and *DHEA *from saliva samples. Salivary hormones provide an unobtrusive way to sample in naturalistic settings. Salivary cortisol and DHEA are highly correlated with serum levels [48,49]. Saliva samples will be collected from each participant at wakening, 30 minutes after wakening, and bedtime over a two-day period (6 samples total) at baseline, 6 and 12 weeks. Cortisol levels will be measured at all 6 time points, while DHEA will be measured only at wakening and bedtime. The saliva samples will be analyzed using enzyme immunoassays for cortisol and DHEA at the STAR (Saliva Testing and Reference) Laboratory, Seattle WA, a CLIA certified laboratory specializing in the analysis of saliva samples.

### Data collection and quality control

We will collect information on the outcomes at every stage of our recruitment, randomization, and treatment processes so that we can report patient flow according to the CONSORT guidelines [50]. Specifically, we will record the number of invitation letters sent, the number of responses received, the resolution of these responses (i.e., ineligible, refused, eligible and randomized, other), the number of participants assigned to each class who actually attended classes and the number of classes they attended, the number of participants in each treatment group providing each type of follow-up data at each follow-up (e.g., questionnaire, saliva samples), the number of withdrawals due to perceived ineffectiveness of the intervention, adverse experiences, loss to follow-up or other causes, and the number of participants completing the trial.

We will implement procedures to ensure that randomization is proceeding as planned, recruitment is on schedule, data collection forms are accurately entered into databases, the computer assisted telephone interviewing (CATI) system is storing data correctly and that data can be accurately transferred and retrieved as needed. We will develop a relational database to track information on every stage of recruitment, randomization, class attendance, and outcomes assessment so we can use standard automated reports of patient flow. All data system processes will be thoroughly tested prior to the start of recruitment.

The CATI programs will contain range and logic checks. Participant attendance information collected during the classes will be double key entered into a database that also contains logic checks. Prior to recruitment, all data systems will be tested with imaginary participants. Data will be examined for completeness using computer programs developed specifically for that purpose. In addition, we will test all analytic programs to ensure that the analyses are accurate.

Saliva samples will be labeled only with unique serial numbers and stored in a secure -70°C freezer until they are assayed at the STAR (Saliva Testing and Reference) laboratory. Samples will be taken to the STAR laboratory periodically in special shipping containers with dry ice to ensure they remain frozen. Standard quality control procedures will be used to ensure assay integrity, including testing all specimens in duplicate wells and using both manufacturer and in-house quality control samples to measure inter-and intra-assay coefficients of variance. Individual samples that exceed a 12% coefficient of variance will be rerun to ensure accurate concentrations are calculated.

In addition, at both Group Health and the STAR laboratory, saliva specimens will be handled and processed only by staff members who are trained and certified by each institution to receive and/or ship biospecimens and who will agree to comply with all institutional policies and procedures to ensure safe handling of the specimens.

To maintain the confidentiality of patient-related information in the database, unique participant study numbers will be used to identify data on treatment and patient outcomes. The password security system will assign appropriate levels of computer privileges to different groups of database users. This will ensure that all masked personnel remain masked to treatment group.

Computer files with participant names will be password protected with access restricted to staff using this information to recruit participants, contact class participants or obtain follow-up data, and interact with any patients reporting adverse events. Any paper data forms, such as home practice logs and saliva logs, will be identifiable only by unique study identification numbers and kept in locked filing cabinets. Finally, all analysis data files will be password protected. Full data back-up procedures will be performed nightly, with partial data back-up throughout the day.

### Protection of human subjects and assessment of safety

#### A. Protection of human subjects

This study was approved by the Human Subjects Review Committee (IRB Number 00000668), which serves as the institutional review board or ethics committee, for Group Health Cooperative. The study will be carried out in compliance with the Helsinki Declaration.

#### B. Safety monitoring

Given the favorable safety profile from previous studies of yoga, a primary care physician experienced in exercise research, independent of the study team, will monitor the safety of participants in this trial. To protect the safety of the study participants, the physician monitor will evaluate new data on adverse-experiences we will provide every six months during the trial. Based on the observed adverse effects of yoga and exercise, the physician montior will make recommendations on a regular basis to the study Principal Investigator and the Office of Clinical and Regulatory Affairs at the National Center for Complementary and Alternative Medicine (NCCAM) regarding continuation, termination, or other modifications of the trial.

#### C. Adverse events

Participants will be asked about adverse experiences at each class and during the 6, 12, and 26-week telephone interviews. We will define an adverse experience as any unfavorable and unintended sign, symptom or disease temporally associated with the use of yoga or therapeutic exercises that could reasonably be related to the interventions. If a participant develops a Serious Adverse Experience (i.e., any adverse event occurring during treatment that results in any of the following outcomes: death, a life-threatening adverse event, inpatient hospitalization or prolongation of existing hospitalization, a persistent or significant disability/incapacity, a congenital anomaly/birth defect, or cancer), it will be promptly (within 7 days) reported to the physician monitor, and if it is at least possibly due to yoga or therapeutic exercise, it will also be promptly reported to the Group Health Human Subjects Review Committee and to NCCAM's Office of Clinical and Regulatory Affairs. In addition, all adverse experiences in the trial will be summarized in routine reports to the physician monitor and the IRB.

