#### D. Stopping rules

No formal stopping rules will be established in advance for efficacy. The trial will be stopped only if the physician monitor believes there is an unacceptable risk of serious adverse events in one or more of the treatment arms. In this case, the physician monitor could recommend terminating one of the arms of the trial or the entire trial.

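### The adverse-experience definition names only yoga and exercise, and enquiry is up to 15 occasions in the class arms against 3 in self care, so safety data for a class arm against self care are not comparable

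*Protocol article*

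**What the plan says.** Under C. Adverse events, an adverse experience is an unfavourable and unintended sign, symptom or disease that is "temporally associated with the use of yoga or therapeutic exercises that could reasonably be related to the interventions". The schedule is: "Participants will be asked about adverse experiences at each class and during the 6, 12, and 26-week telephone interviews". Table 4 lists adverse experiences at all three follow-ups without restriction by arm.

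A serious adverse experience is "any adverse event occurring during treatment that results in any of the following outcomes", followed by a list of outcomes such as death and hospitalization. Each goes to the physician monitor within 7 days; "if it is at least possibly due to yoga or therapeutic exercise, it will also be promptly reported" to the review committee and the funder's regulatory office. All adverse experiences are also summarized routinely for the monitor and the review board.

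On the treatments: "Both the yoga and exercise interventions will consist of 12 weekly 75-minute classes supplemented by home practice". For self care: "Participants in this group will be mailed a copy of" a book, whose contents include "initiating a comprehensive fitness and strength program".

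B. Safety monitoring bases the monitor's recommendations on observed adverse effects of yoga and exercise. D. Stopping rules refers to "unacceptable risk of serious adverse events in one or more of the treatment arms" and lets the monitor recommend ending one arm or the whole trial.

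**The concern.** Three features of the same section treat the self-care arm differently from the class arms.

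- **Definition.** The event must go with use of yoga or therapeutic exercise and be plausibly related to the interventions. A back flare or a strain in a self-care participant does not meet this wording unless that person happened to use yoga or such exercises. Because relatedness decides whether an event is counted at all, unrelated events are not counted as adverse experiences in any arm.
- **Enquiry.** Only participants with classes can be asked at classes.
- **Serious-event window.** The restriction to treatment has no stated meaning for a mailed book, and it is not said whether it covers the weeks after the last class.

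What is at stake is the reading of the safety tables. If all collected reports are tabulated by arm, the class arms will tend to show more events than self care even where true risks are equal. The physician monitor may act on a single arm, and the background against which to judge that arm is collected under different rules.

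**Working it through.** The article states no safety rate, safety power or safety comparison, so there is no figure of its own to reproduce. The check is a count, an illustration and a reading of the wording.

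**1. Scheduled enquiries per participant**

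Inputs: 12 classes in each class arm and none in self care (Study treatments); 3 interviews in every arm (C. Adverse events, Table 4).

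- Yoga or exercise, full attendance: 12 + 3 = 15
- Self care: 0 + 3 = 3
- Ratio: 15 / 3 = 5
- Interviews only: 3 against 3
- Yoga against exercise: 15 against 15

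**2. What unequal enquiry alone could do**

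Assumptions, none of them in the article: each enquiry has the same chance q of yielding a report in every arm, and enquiries are independent. The definition is ignored here, so that only the frequency of asking differs. Then P(at least one report) = 1 − (1 − q)^k, with k = 15 or 3. Group sizes are 210 × 2/5 = 84 and 210 × 1/5 = 42.

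| Assumed q | Class arm, k = 15 | Self care, k = 3 | Chance of two-sided p < 0.05, 84 v 42 |
|---|---|---|---|
| 0.02 | 1 − 0.98^15 = 26.1% | 1 − 0.98^3 = 5.9% | about 0.83 |
| 0.05 | 1 − 0.95^15 = 53.7% | 1 − 0.95^3 = 14.3% | above 0.99 |
| 0.10 | 1 − 0.90^15 = 79.4% | 1 − 0.90^3 = 27.1% | about 1.0 |

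This takes every extra enquiry as a full extra chance to report. If participants recalled at interview everything that they would have said in class, the frequency of asking would make no difference. The truth lies somewhere between, and the direction is always towards more reports in the class arms.

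**3. The definition, clause by clause**

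- Non-serious event in a class arm: meets the definition if it goes with use of the classes or home practice and could be related.
- Non-serious event in self care: the book is neither yoga nor, in the article's terms, the therapeutic exercise intervention. Literally it is not counted, even if it follows the program that the book describes. Whether a participant's own exercising would qualify is left open.
- Serious event in any arm: the clause speaks of any adverse event and treats relation to yoga or exercise as a second step that governs onward reporting. The narrower definition need not apply here.

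**4. The serious-event window**

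Classes are 12 weekly sessions and follow-up ends at week 26, which leaves 26 − 12 = 14 weeks whose status is unclear in the class arms. Home practice is part of the intervention and is still recorded at week 26 (Table 4), which supports a longer window; the end of classes supports a shorter one. For self care no period is stated at all.

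**The case against.** The strongest reply is that the article promises no safety comparison between arms. The aims and the statistical analysis section contain none, monitoring is directed at yoga and exercise, and asking at each class protects participants. That stands: this is a weakness of definition and ascertainment, not a contradiction of a planned analysis.

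Four stronger readings are tempting, and the article does not support them.

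- **A reader might infer that self-care events can never be recorded.** The three interviews cover every arm, and a serious self-care event can be read as reportable to the monitor.
- **A reader might infer that no fair safety comparison can be made.** Yoga against exercise has the same definition, the same number of classes and the same interviews. An interview-only comparison with self care would also be fair once the definition is neutral to arm.
- **A reader might set the self-care count to zero, give yoga an assumed event rate and test the difference.** That is circular. It lets the definition remove every event in one arm and none in the other. It also counts events of any severity, whereas stopping turns on serious ones, and a death or hospitalization depends far less on how often people are asked.
- **A reader might infer that weeks 13 to 26 lie outside the serious-event window.** That is one reading only, and an article may leave the exact window to the full protocol.

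It is also true that worsening of back symptoms is visible elsewhere. The RDQ, bothersomeness, disability days and medication use are collected in all arms at 6, 12 and 26 weeks by interviewers unaware of assignment. Those measures do not capture injuries or other events, and they do not repair the adverse-experience counts.

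**Conclusion.** The point holds for class arms against self care. As written, the definition leaves most non-serious self-care events uncounted, and scheduled enquiry differs by up to 5 to 1. Both push in the same direction. The 15 and 3 follow from the text, assuming full attendance; the percentages in the illustration rest on assumed reporting chances and independence, and show what could happen rather than what will.

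The window for serious events is a lesser, related point: it is not stated for the book and is ambiguous after week 12 for the classes, while the stopping section speaks of serious-event risk in any arm. Nothing calculated here shows that a decision to stop an arm would be wrong.

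Yoga against exercise and the efficacy analyses are unaffected. The section should be corrected, because the definition decides what is counted and events left uncounted may not be recoverable afterwards.

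**What to change.** 1. Define an adverse experience in the same words for all three arms, as any unfavourable and unintended sign, symptom or disease since the last contact, and record relatedness in a separate field.
2. Base any comparison with self care on the 6-, 12- and 26-week interviews, which are common to all arms. List events reported in class separately; they remain useful to the monitor.
3. State one observation window for serious events, the same in every arm: randomization to week 26.

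The interviews already exist, so the cost is wording in the protocol and on the forms. The downside is that the physician monitor will have more reports to read, many of them unrelated to treatment.
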